## I. Research Background and Significance

Gastrointestinal endoscopy plays an irreplaceable role in the diagnosis and treatment of gastrointestinal diseases. With the continuous pursuit of comfortable medical care, the demand and requirements for painless gastrointestinal endoscopy are increasing. The commonly used sedative anesthetic drugs currently have significant inhibitory effects on hemodynamics and respiration, leading to a higher incidence of sedation-related adverse events [1]. Propofol and etomidate are currently commonly used drugs for sedation in gastrointestinal endoscopy, but both may cause adverse events such as hypoxemia, hypotension, myoclonus, and injection pain [2-3]. Remimazolam is a new type of benzodiazepine drug, characterized by rapid onset and rapid metabolism, with a lower incidence of hemodynamic and respiratory-related adverse events compared to propofol and etomidate [4-6]. However, remimazolam alone requires a higher dose to meet sedation/analgesia requirements, and under high-dose conditions, hemodynamic instability and respiratory depression can still occur. Optimizing drug use by combining the advantages and disadvantages of the three drugs is the main purpose of this study. Therefore, this study aims to evaluate the efficacy of remimazolam combined with etomidate or propofol for sedation/analgesia in painless gastrointestinal endoscopy, providing a safer and more optimal drug regimen for clinical use.

## II. Research Objectives

To evaluate the clinical efficacy of remimazolam combined with etomidate or propofol for painless gastrointestinal endoscopy.

## III. Research Design

### 1. Study Design

This study is a single-center, double-blind, randomized controlled clinical trial. Written informed consent must be obtained from participants before any trial procedures are conducted.

### 2. Study Population

Inclusion Criteria:

1. Age > 18 years, scheduled for gastrointestinal endoscopy under procedural sedation;
2. ASA I-III.

Exclusion Criteria:

1. Refusal to sign the informed consent;
2. Severe respiratory depression;
3. Acute or severe bronchial asthma;
4. Known or suspected gastrointestinal obstruction;
5. Known allergy to any of the drugs or components used in this study;
6. Severe liver or kidney dysfunction;
7. Long-term use of opioid drugs;
8. Long-term use of benzodiazepines;
9. Anticipated difficult airway;
10. Adrenal insufficiency.

#### Exclusion Criteria During the Study:

1. Unexpected events during sedation/analgesia or surgery;
2. Participants who withdraw from the study on their own;
3. Loss to follow-up.

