#### 3. Randomization and Blinding

Researchers will use the website ([www.random.org](http://www.random.org)) to generate a block randomization scheme. All participants will be randomly assigned to receive remimazolam combined with etomidate or propofol for sedation/analgesia in a 1:1 ratio. The participants, anesthesiologists, endoscopists, and postoperative evaluators will be blinded to the group assignments. The anesthesiologist will be responsible for intraoperative and postoperative assessments. The group assignments will not be blinded to the anesthesia nursing staff who prepare the anesthetic drugs.

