The anesthesia nursing staff will prepare the sedation/analgesia drugs according to the group assignment. Remimazolam tosylate (RT) will be diluted with normal saline to 1.25 mg/mL, and individualized dosing will be administered based on patient weight. All patients will receive lidocaine gel for pharyngeal surface anesthesia before undergoing gastroscopy. Oxygen will be administered via an endoscopic mask at 6 L/min from the start of the endoscopic procedure until the patient is fully awake. According to the expert consensus on sedation/analgesia for gastrointestinal endoscopy, remimazolam will be administered as a single intravenous (IV) bolus over 1 minute using a micro-infusion pump. The initial loading dose of remimazolam will be 0.15 mg/kg, combined with etomidate 0.1 mg/kg or propofol 0.75 mg/kg, and sufentanil 5-10 mcg. The analgesic drug will be administered 3 minutes before the sedative drug. When the patient is sufficiently sedated (Modified Observer's Assessment of Alertness/Sedation [MOAA/S]  $\leq 3$ ), the endoscopic examination will commence. If sedation is deemed inadequate or intubation fails, up to 5 supplemental doses (RT 2.5 mg) of intravenous bolus can be administered at 1-minute intervals within 15 minutes after the initial dose. If the initial dose and supplemental doses are insufficient to achieve adequate sedation for endoscopic insertion, the anesthesiologist will decide whether to administer a rescue sedative drug (propofol 0.75 mg/kg) at the start of the procedure. Once the procedure begins, to maintain an adequate level of sedation throughout the examination (MOAA/S score  $\leq 3$ ), supplemental doses of remimazolam will be administered to the patient at least 1-minute intervals (not exceeding 5 supplemental doses in total) based on the anesthesiologist's judgment. If these doses are insufficient to maintain appropriate sedation, a rescue sedative drug will be administered to complete the examination. If the use of rescue drugs raises safety concerns, the examination can be completed under general anesthesia with endotracheal intubation.

Throughout the procedure, the level of sedation will be assessed using the MOAA/S score. The anesthesiologist, who is blinded to the group assignment, will be responsible for the MOAA/S scoring. Before enrolling patients in this study, the evaluating physician will complete at least one training session to standardize the MOAA/S scoring. The MOAA/S score will be recorded at the

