## 5. Observation Indicators

### Primary Outcome:

The primary outcome is the incidence of respiratory depression (RD). Respiratory depression is defined as a respiratory rate  $< 8$  breaths per minute and/or  $SPO_2 < 90\%$  [7]. Respiratory rate will be monitored using end-tidal carbon dioxide monitoring. When a decrease in respiratory rate or oxygen saturation occurs, the anesthesiologist will need to assess the accuracy of the values to ensure normal readings. If airway obstruction due to tongue base retraction is relieved by airway maneuvers and the respiratory rate is above the assessment threshold, it will not be judged as respiratory depression, but the number of airway maneuvers will be recorded.

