### Secondary Outcomes:

Secondary outcomes mainly include the incidence of intraoperative hypoxemia ( $SPO_2 < 90\%$ ,  $> 10s$ ), the number of minor airway maneuvers (such as jaw lift, patient repositioning, mask ventilation), the lowest  $SpO_2$ , the number of times the endoscope is removed due to persistent hypoxemia, and the success rate of sedation/analgesia (i. Completion of the entire endoscopic procedure; ii. No need for alternative and/or rescue sedatives; iii. Up to 5 supplemental doses administered within 15 minutes after the initial dose).

The examination time (from intubation to removal of the endoscope), sedation/analgesia time (from administration of analgesic drugs to full awakening), and awakening time (from administration of flumazenil to full awakening) will be recorded. The number of sedative drug supplements, the dose of sedative drugs used, and the dose of analgesic drugs used will be recorded. Vital signs (MAP, HR,  $SPO_2$ ) at different time points will be recorded. After the patient is fully awake, the occurrence of nausea and vomiting will be recorded. After the examination, the endoscopist's satisfaction will be recorded. The endoscopist will subjectively evaluate based on the operating conditions and whether the operation was interrupted, with a full mark of 10 points, 0-3 points for dissatisfaction, 4-7 points for relative satisfaction, and 8-10 points for satisfaction.

On the first postoperative day (postoperative Day 1, POD1), patient satisfaction will be recorded. Patients will subjectively evaluate based on their own feelings. Similarly, the full mark is 10 points,

with 0-3 points indicating dissatisfaction, 4-7 points indicating relative satisfaction, and 8-10 points indicating satisfaction. The occurrence of nausea and vomiting, itching, and urinary retention will be recorded.

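### Excluding randomised patients for undefined unexpected events during sedation, or for loss to follow-up, can remove primary-outcome events and discards primary data already observed

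*Protocol*

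**What the plan says.** Section III.2 of the protocol (Study Population) has two sets of exclusions. The first is the usual eligibility list. The second, headed "Exclusion Criteria During the Study", has three items: "Unexpected events during sedation/analgesia or surgery", "Participants who withdraw from the study on their own" and "Loss to follow-up". None of the three is defined further.

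Four other parts of the protocol bear on how this list works:

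- **Primary Outcome (III.5).** RD is a respiratory rate below 8 per minute and/or SpO2 below 90%. It is assessed by the anesthesiologist from the monitoring used for the procedure.
- **Study Interventions (III.4).** Rescue sedation is foreseen. If rescue raises a safety concern, "the examination can be completed under general anesthesia with endotracheal intubation".
- **Secondary Outcomes (III.5).** Endoscope removals for persistent hypoxemia are counted, and sedation success depends partly on completing the examination without rescue. The only contact after the procedure is the next day: "On the first postoperative day (postoperative Day 1, POD1), patient satisfaction will be recorded", together with nausea and vomiting, itching and urinary retention.
- **Sample Size Calculation (V.1).** It assumes 30% RD with propofol, a halving with etomidate, 118 per group, and 124 after a 5% dropout allowance.

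**The concern.** An event during sedation can only happen after the allocated drug has been given, so item 1 selects patients on something the treatment may have caused. It also covers the same minutes as the primary outcome. Severe RD, conversion to intubation or an abandoned examination could each be called unexpected, and no sentence says they are not. A patient excluded for such an event leaves both the numerator and the denominator of the primary outcome.

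Item 3 works differently. RD status is known once the procedure and awakening are over. A patient who cannot be reached the next day has a complete primary outcome, and excluding that patient discards it for no gain. This biases the comparison only if loss is related to both arm and outcome; otherwise it just wastes data. The same holds for item 2 when a patient withdraws after the examination.

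This is not a complaint about an analysis set missing from the protocol. It concerns a rule the protocol states, and a statistical analysis plan that kept these patients would contradict it.

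**Working it through.** **1. The planned sample size reproduces.** Inputs from V.1 and V.2: 30% versus 15%, two-sided α = 0.05, power 0.80 (printed as the value of β). With unpooled variance:

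n = (1.960 + 0.842)² × (0.30 × 0.70 + 0.15 × 0.85) / 0.15² = (2.802)² × 0.3375 / 0.0225 ≈ 117.7, so 118 per group.

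The dropout step gives 118 × 1.05 = 123.9, so 124. The sample size is not where the problem lies.

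**2. Effect of removing RD cases.** Let p be the true RD risk in an arm and f the share of its RD cases excluded. The protocol gives no value for f, so every f below is an assumption.

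- Observed rate: p′ = p(1 − f) / (1 − pf)
- Patients remaining: n′ = 124(1 − pf)

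Rejection probabilities come from exact enumeration of the two-sided Pearson chi-square test, with n′ rounded to whole patients.

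**3. Same share excluded in both arms, true rates 30% versus 15%**

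| f in both arms | Observed rates | n remaining | RD cases removed | Power |
|---|---|---|---|---|
| 0 | 30.0% vs 15.0% | 124 / 124 | 0 / 0 | 82% |
| 10% | 27.8% vs 13.7% | 120 / 122 | 3.7 / 1.9 | 78% |
| 25% | 24.3% vs 11.7% | 115 / 119 | 9.3 / 4.6 | 72% |

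Worked example at 25%, propofol arm: p′ = 0.30 × 0.75 / (1 − 0.075) = 0.225 / 0.925 = 0.243, and n′ = 124 × 0.925 = 114.7.

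The absolute difference shrinks from 15.0 to 12.6 points at f = 25%. The odds ratio does not move (0.41 throughout), and the risk ratio moves slightly away from 1 (0.50 to 0.48). With 30% in both arms and 25% of cases excluded in each, the rejection rate is 5.1%. Equal exclusion therefore costs power but does not inflate type I error.

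**4. Different shares excluded, no true difference (30% in both arms)**

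| Shares excluded | Observed rates | RD cases removed | False-positive rate |
|---|---|---|---|
| 15% vs 10% | 26.7% vs 27.8% | 5.6 / 3.7 | about 5.5% |
| 20% vs 10% | 25.5% vs 27.8% | 7.4 / 3.7 | about 7% |
| 30% vs 10% | 23.1% vs 27.8% | 11.2 / 3.7 | about 13% |
| 40% vs 10% | 20.5% vs 27.8% | 14.9 / 3.7 | about 25% |

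**5. Scale against the dropout allowance.** The allowance is 124 − 118 = 6 per arm for all causes. Losing 10% of RD cases in both arms stays inside it. The larger shares, from 9 removed in one arm upward, exceed it and would show as unusually high dropout.

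**The case against.** A reader might infer that the rule does remove RD cases and so does bias the result. The text does not support that. It nowhere says RD is an unexpected event, and much of the protocol points the other way. RD is the primary outcome with an expected rate of 30% in one arm. Rescue and intubation are foreseen, endoscope removals for hypoxemia are counted, and RD appears among the defined adverse events in section IV. The more coherent reading is that unexpected means something outside these listed events. That objection stands, and it limits the point to what the rule can do.

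It can also be argued that the list governs stopping participation, not analysis. This is weaker. Loss to follow-up cannot stop a single-session sedation that has already ended, so an exclusion on that ground makes sense only as removal from the data.

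The larger scenarios are assumed, and no figure in the protocol supports a 40% versus 10% imbalance. At small imbalances the effect on type I error is slight. This stands too, which is why the small cases are shown beside the large ones.

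Finally, section III.3 states that the anesthesiologist making the assessments is blinded. That limits deliberate selection. It does not prevent bias when one regimen itself causes more of the events that lead to exclusion.

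**Conclusion.** The protocol states an undefined post-randomisation exclusion that overlaps in time with the primary outcome and exempts none of that outcome's consequences. Followed as written, it can remove RD cases, and it can bias the comparison in either direction if exclusion differs by arm. Separately, exclusion for loss to follow-up discards primary outcomes that have already been observed.

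The size cannot be derived from the protocol. Under the planned rates and the assumed shares, power falls from 82% to 78% or 72% when 10% or 25% of RD cases are lost equally. With no true difference, the false-positive rate is about 7%, 13% or 25% when 20%, 30% or 40% of cases are lost in one arm and 10% in the other. No bias has been quantified for loss to follow-up. The direction of any bias is unknown.

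**What to change.** Rewrite the list of exclusions during the study in one paragraph:

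- Separate stopping study participation from exclusion from analysis, and remove items 1 and 3 as grounds for the latter.
- Analyse the primary outcome in all randomised patients who received any study sedative, in the assigned arm. This includes patients with unexpected events, rescue, intubation or an incomplete examination.
- Score RD by the existing definition in III.5 on the data observed. Intubation should not become a new component of the endpoint.
- Reword item 2 so that data up to withdrawal are used as far as consent permits.
- State that missing day-1 data affect only the day-1 outcomes.

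The cost is a short amendment, which section VI.1 requires to go to the ethics committee. It needs no extra patients or data. Observed RD rates may be somewhat higher than under the exclusions.

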#### 3. Randomization and Blinding

Researchers will use the website ([www.random.org](http://www.random.org)) to generate a block randomization scheme. All participants will be randomly assigned to receive remimazolam combined with etomidate or propofol for sedation/analgesia in a 1:1 ratio. The participants, anesthesiologists, endoscopists, and postoperative evaluators will be blinded to the group assignments. The anesthesiologist will be responsible for intraoperative and postoperative assessments. The group assignments will not be blinded to the anesthesia nursing staff who prepare the anesthetic drugs.

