#### 4. Study Interventions

Before sedation/analgesia for gastrointestinal endoscopy, all participants will undergo preoperative evaluation at the anesthesia clinic. Baseline data will be collected, including age, gender, height, weight, ASA classification, Mallampati classification, drinking history, surgical history, comorbidities (hypertension, diabetes, cerebrovascular disease, cardiovascular disease, liver and kidney diseases), and PRODIGY score [7]. Patients will be fasting for 6 hours and no fluids for 2 hours before the procedure. Upon entering the operating room, patients will be positioned according to the type of examination, and monitoring devices will be connected to record baseline vital signs

(non-invasive blood pressure, oxygen saturation, ECG, end-tidal carbon dioxide). Preoxygenation with an endoscopic mask (8-10 L/min, 3-5 min) will be performed under spontaneous breathing, and intravenous access will be established. Resuscitation drugs such as epinephrine, atropine, ephedrine, and phenylephrine will be prepared.

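### Procedure type is neither a stratification factor nor a named baseline variable, which leaves small, avoidable chance variation in outcomes likely to depend on it

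*Protocol*

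**What the plan says.** **Eligibility.** Protocol III.2 (Study Population) takes adults "scheduled for gastrointestinal endoscopy under procedural sedation" with ASA class I to III. It sets no limit by type of examination.

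**Signs that procedures vary.** Protocol III.4 (Study Interventions) states that "patients will be positioned according to the type of examination", and ties one preparation step to a single procedure: "All patients will receive lidocaine gel for pharyngeal surface anesthesia before undergoing gastroscopy".

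**Allocation.** Protocol III.3 (Randomization and Blinding): "Researchers will use the website ([www.random.org](http://www.random.org)) to generate a block randomization scheme", with patients assigned "for sedation/analgesia in a 1:1 ratio". No stratification factor is named.

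**Baseline data.** The list in III.4 covers demographics, ASA and Mallampati class, drinking and surgical history, comorbidities and the PRODIGY score. Procedure type is not named, although the list is worded as open-ended.

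**Outcomes.** The primary outcome is respiratory depression (III.5). Sedation success requires a completed examination without rescue sedation and carries the limit "Up to 5 supplemental doses administered within 15 minutes after the initial dose". Examination time, sedation time, number of supplements and doses are also recorded.

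**Analysis.** V.2 plans two-group comparisons (t-test or Mann-Whitney; chi-squared or Fisher's exact test) with no adjustment.

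**The concern.** The primary outcome is respiratory, and an endoscope passed through the pharynx shares the airway in a way that a colonoscope does not. Position may differ too. Respiratory risk is therefore likely to depend on the procedure. Sedation success is also exposed: its cap on supplements is fixed and not scaled to procedure length, so a longer examination is more likely to fail it whatever the drug. Supplement counts and total dose depend on length in the same way.

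Where a strong predictor of outcome is known before allocation and is neither balanced nor used in the analysis, its chance imbalance adds noise to the treatment comparison. If it is not recorded, that imbalance cannot be shown by arm or adjusted for later. At stake are some precision and the ability to report procedure mix, not the validity of the test.

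**Working it through.** **1. The plan's own sample size.** Inputs from V.1: 30% v 15% (a 50% relative reduction), alpha 0.05, and power 0.80 (printed as beta = 0.8); V.2 makes tests two-sided. With the unpooled formula:

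n = (1.960 + 0.842)² × (0.30×0.70 + 0.15×0.85) / 0.15² = 7.849 × 0.3375 / 0.0225 = 117.7, so 118 per arm.

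118 × 1.05 = 123.9, so 124. Both stated figures reproduce. Stratification would not change them.

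**2. Chance imbalance in procedure mix.** The protocol gives no mix, so the share p of one procedure type is an assumption. For n per arm, SD of the difference in shares = sqrt(2p(1−p)/n).

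| n per arm | p | SD (points) | 95% range (points) | P(gap > 10 points) |
|---|---|---|---|---|
| 124 | 0.5 | 6.4 | ±12.4 | 11.5% |
| 124 | 0.3 or 0.7 | 5.8 | ±11.4 | 8.6% |
| 118 | 0.5 | 6.5 | ±12.8 | 12.4% |
| 118 | 0.3 or 0.7 | 6.0 | ±11.7 | 9.4% |

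**3. Effect on the primary risk difference.** Shift = imbalance × gap in respiratory depression between procedure types. The gap is assumed. With p = 0.5, n = 124 and the imbalance at the edge of its 95% range (0.1245):

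- gap 10 points: 0.1245 × 10 = 1.2 points
- gap 20 points: 2.5 points
- gap 30 points: 3.7 points

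The planned effect is 15 points. The formula takes the same gap in both arms. If the new combination halves risk in each class and the quoted gap is the control-arm gap, the mean gap is three quarters of it and the shifts shrink in proportion (3.7 becomes 2.8).

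**4. Set against ordinary sampling error.** At 30% v 15% with 124 per arm, SE of the risk difference = sqrt(0.3375/124) = 5.2 points, a 95% half-width of 10.2. The SD of the procedure-mix shift is 0.0635 × gap, which is 0.6 points for a gap of 10 and 1.9 for a gap of 30. Its share of the variance is (0.635/5.217)² = 1.5% and (1.905/5.217)² = 13%. This component already sits inside the unadjusted standard error.

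**5. Type I error and power.** Simulated with 118 per arm, a 50:50 mix, 30% overall control risk, and risk halved in each class under the alternative (at least 100,000 trials per setting):

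| Control risk by class | Gap | Type I error, unstratified chi-squared | Power, unstratified chi-squared | Power, unstratified lists with Cochran-Mantel-Haenszel (CMH) test | Power, stratified lists with CMH test |
|---|---|---|---|---|---|
| 37.5% / 22.5% | 15 | 0.051 | 0.798 | 0.802 | 0.805 |
| 40% / 20% | 20 | 0.052 | 0.797 | 0.808 | 0.810 |
| 45% / 15% | 30 | 0.050 | 0.797 | 0.823 | 0.827 |

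With stratified lists the CMH test holds type I error at about 0.050. Stratified lists followed by an unadjusted chi-squared test become conservative (0.045 at a gap of 20, 0.039 at 30), so lists and test should be changed together.

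**6. Sedation success.** The same formula applies, but the protocol gives no success rate by procedure. For assumed gaps of 10 to 35 points, the edge-of-range shift is 1.2 to 4.4 points.

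**The case against.** Stratification is optional. A single-centre trial with 1:1 block randomisation is valid without it; chance imbalance is sampling error, already counted in the confidence interval and the 5% test level. That stands in full, and step 5 confirms it.

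The procedure mix and the risk gaps are not in the protocol. That also stands, so the sizes are given as ranges under stated assumptions.

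The mix might be narrower than it looks. Outside the reference list colonoscopy is never named, and the lidocaine sentence could be read as every patient having a gastroscopy. But III.2 states no such limit, and positioning by type of examination would be odd wording if there were only one type. The protocol is likewise silent on the number of lists, so a single unstratified list is the natural reading rather than a stated fact.

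A stratified or adjusted analysis could sit in a statistical analysis plan that is not shown. True of the analysis. Stratified allocation, however, must be fixed before enrolment, and an analysis plan can use procedure type only if it was recorded.

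A reader might infer that drug effect and case mix cannot be told apart, or that airway risk and duration go unseen. The documents do not support this. A shift of 1 to 4 points cannot pass for a 15-point effect. Examination and sedation times are recorded for each patient, although after allocation, so they are not clean baseline covariates. Anticipated difficult airway is excluded, and Mallampati class, PRODIGY score and airway manoeuvres are recorded; these cover the patient's risk rather than the procedure's. The baseline list is open-ended, so procedure type may well be collected. What is missing is the commitment.

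**Conclusion.** The point holds as a modest, inexpensive improvement, not as an error or a bias. Eligibility is open across procedure types, the protocol itself indicates that procedures vary, and procedure type is neither a named stratification factor, nor a named baseline item, nor part of the stated analysis.

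Under an assumed 50:50 mix, the arms' shares could differ by about ±12.4 points by chance. With assumed gaps of 10 to 30 points in respiratory depression, that moves the risk difference by about 1.2 to 3.7 points at the edge of the range, and usually by less. Type I error is unaffected. The stratified approach gains roughly 0.5 to 3 points of power for gaps of 15 to 30 points. If the mix is nearly uniform, or risk hardly depends on procedure, the gain is close to nil, but recording the class still lets readers see the mix.

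**What to change.** 1. In III.4, name procedure class as a baseline variable (gastroscopy only, colonoscopy only, both or other), fixed from the scheduled procedure before allocation, and report it by arm. This is the firm request. If only one type of examination is meant to be eligible, say so in III.2 and the point falls away.
2. In III.3, generate a separate 1:1 block list within each class.
3. Compare the primary outcome and sedation success with a Mantel-Haenszel risk difference or a Cochran-Mantel-Haenszel test over the classes, here or in the statistical analysis plan. Do not stratify the lists and keep the unadjusted test.
4. If enrolment has begun, leave the randomisation alone, record the class and use the stratified analysis. In the simulations this alone gave most of the gain: 1.1 of 1.3 power points at a gap of 20, and 2.6 of 3.0 at a gap of 30.

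Cost: one more form field, three lists instead of one, and slightly more allocation handling for the nursing staff who prepare the drugs. No extra patients are needed, and 118 and 124 per arm stay as they are.
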